## Abstract

**Background:**

Thalamic hemorrhage (TH) is a neurological insult with a high rate of morbidity and mortality. Moderate TH (10–30 ml) accounts for more than half of all TH. Treatment remains controversial. The role of acupuncture in patients with moderate TH is not clear.

**Methods:**

We will conduct a single-center, randomized, parallel group, and assessor-blinded clinical trial. A total of 488 patients with moderate TH will be randomly assigned to one of eight groups: 10–15 cc left sided TH study group (*N* = 61) and a corresponding control group (*N* = 61), 10–15 cc right sided TH study group (*N* = 61) and a corresponding control group, 15–30 cc left sided TH study group (*N* = 61) and a corresponding control group (*N* = 61), and 15–30 cc right sided TH study group (*N* = 61) and a corresponding control group. Study groups will receive acupuncture in addition to standard treatment, while control groups will receive standard treatment alone. The primary outcome will be change in National Institutes of Health Stroke Scale scores at 30 and 90 days after TH. The secondary outcomes will be death or major disability, defined as a score of 3 to 6 on the modified Rankin scale (in which a score of 0 indicates no symptoms, a score of 5 indicates severe disability, and a score of 6 indicates death) at 90-days, need for surgery at 30-days, Glasgow Outcome Scale (GOS) score at 90-days following TH onset, and the results of several additional group specific tests. The rate of adverse events will then be compared between the groups.

**Discussion:**

This study will attempt to answer the question of whether or not acupuncture can improve neurologic outcome following moderate TH.

**Trial registration:**

Chinese clinical trial registry (ChiCTR-IOR-16008362)

## Background

Spontaneous intracerebral hemorrhage (ICH), non-iatrogenic ICH without trauma, is the second most common and the most devastating form of all strokes with the poorest prognosis [1, 2]. Approximately 15% of all cases of spontaneous ICH occur in the thalamus [3–5]. The thalamus is a deep brain structure and is an important center for the transmission of neural signals [3, 6]. Due to its anatomical location and the vital functions that it performs, the decision of conservative or surgical management for TH remains controversial [2, 7, 8]. Management is influenced mainly by the clinical experience of the treating surgeon and the volume of the hematoma [9]. Patients with minor TH, especially volumes less than 10 cc, usually obtain favorable outcomes when treated with conservative measures. However, patients with major TH, greater than 30 cc, have mortality rates of more than 80%, no matter what treatment is selected [10]. Moderate TH (10–30 mL) constitutes more than half of all cases of TH, and these patients have a mortality rate of more than 30% [11]. As moderate TH is the most common form of TH, its prognosis carries the greatest weight in calculating the prognosis of all forms of TH. In patients with moderate TH, conservative treatment alone versus surgical treatment is naturally a difficult decision to make. Because surgical treatment is invasive, adjacent structures may be damaged and neural pathways may be disrupted during surgical evacuation of a hematoma, thereby aggravating the degree of neurologic deficits or creating new ones. Meanwhile, conservative treatment alone does not offer the involved thalamic tissue the same type of relief that evacuation offers and is therefore felt to be a limited strategy in improving neurologic function. The limitations of both therapeutic strategies provide considerable room for better approaches or combinations of approaches.

Two recognized mechanisms of brain injury from ICH have been established [12, 13]. Primary injury happens at the time of initial hemorrhage when direct damage to brain tissue occurs either secondary to the hematoma itself or to its mass effect on surrounding brain tissue. Secondary injury happens at some time following initial hemorrhage and includes neuronal death from either the inflammatory response to the hematoma, the release of toxic materials and other cytokines, the breakdown of the brain blood barrier, apoptosis, or the development of edema. While the pathophysiology of ICH provides many potential approaches for its treatment, enlargement of the hematoma and the development of surrounding edema have been identified as major contributors to the high morbidity and mortality of ICH and have thus been the major focus of potential treatment strategies [14–17].

Acupuncture, one of the major branches of Traditional Chinese Medicine (TCM), has long been used to treat acute stroke, including hemorrhagic stroke, in China as well as in many other East Asian countries. Acupuncture’s utility in the treatment of non-hemorrhagic stroke, which is now documented by the WHO (World Health Organization, 2002), has been widely researched [18]. In recent years, a number of studies using modern technologies have shown that acupuncture may have neuroprotective effects following hemorrhagic stroke as well [19–22]. One preclinical systematic review of 19 animal studies showed that GV20 (Baihui) based acupuncture can improve neurologic outcome by regulating the inflammatory response to a hematoma, inhibiting neuronal apoptosis, reducing cerebral edema, maintaining ATP supply, promoting nerve regeneration, maintaining neuronal membrane integrity, and promoting hematoma resorption [23]. In another animal study, acupuncture at the DU20 acupoint was reported to have a neuroprotective effect on cerebral hemorrhage by inhibiting Notch-Hes signaling in rat basal ganglia [24]. It has also been reported that electro-acupuncture treatment at the Zusanli (ST36) acupoint may accelerate ICH-induced angiogenesis via the up-regulation of the HIF-1α protein and therefore may enhance recovery following hemorrhagic cerebral injury [25]. A separate study confirmed that treatment at the ST36 acupoint may aid recovery following central nervous system intracerebral hemorrhage in rats [26]. Although animal studies have led to progress in determining how acupuncture exerts its benefits in the treatment of acute hemorrhagic stroke, the determination of its clinical value remains incompletely assessed [27–30].

To our knowledge, no organized study has reported on the effects of acupuncture in patients with acute moderate TH. Specifically, no prior study has examined whether or not the use of acupuncture combined with conventional treatments improves the prognosis of moderate TH patients compared to conventional treatments alone.

## Methods/Design

### Aims

We hypothesize that the addition of acupuncture to conventional treatments will improve neurological prognosis in TH patients. To test this hypothesis, we will compare study and control groups created based on the size and side of the TH. The study groups will receive acupuncture in addition to standard treatments, while the control groups will receive standard treatments alone.

### Study design

This study will be a single-center, randomized, placebo-controlled, parallel group, and patient-assessor-blinded clinical trial. After completing informed consent, 488 eligible patients will be recruited and randomized to one of eight groups: 10–15 cc left sided TH study group (*N* = 61) and a corresponding control group (*N* = 61), 10–15 cc right sided TH study group (*N* = 61) and a corresponding control group, 15–30 cc left sided TH study group (*N* = 61) and a corresponding control group (*N* = 61), and 15–30 cc right sided TH study group (*N* = 61) and a corresponding control group. The patients in each of the study groups will receive 36 sessions of Chinese acupuncture in addition to standard treatments for TH, which include anticonvulsant therapy, antihypertensives, osmotic diuretics for the management of intracranial pressure, and invasive treatments as necessary. The patients in each of the control groups will receive standard treatments only. Patients’ neurologic status will be assessed at baseline and at the end of treatment as well as at 30 day and 90 day follow-up intervals. CT imaging will be performed on admission and at 90 days follow up. All patients will be required to complete written informed consent prior to enrollment. If patients are unable to complete written informed consent, it will be obtained from their relatives. A flow chart demonstrating an outline of the study is included in Fig. 1.

**Fig. 1 Fig1:**
[figure not shown]
The flow chart. Patients in acupuncture group will receive 36 sessions acupuncture treatment, 6 days a weeks for 6 weeks, in addition to conventional treatments and patients in control group will receive conventional TH treatments only. LSTH, left-sided thalamic hemorrhage; RSTH, right-sided thalamic hemorrhage

### Study setting

This study will be conducted on a neurosurgery unit in Sichuan University’s West China (Hua Xi) Hospital in Chengdu, China. With 4300 beds and more than 300 surgical operations per day, the hospital is one of the largest in China. The neurosurgery department is the largest in southwest China, with 181 surgical beds, 100 beds for rehabilitation and/or postoperative recovery, and more than 3800 craniotomies performed per year.

### Ethics

This trial will be carried out in accordance with the ethical standards described in the 2013 updated Declaration of Helsinki. The study was approved by the West China Hospital, Sichuan University clinical research and biomedical ethics committees (ethics reference: 2016-044). Written and signed informed consent will be obtained from all participants prior to their inclusion in the study. This trial has also been registered on www.chictr.org.cn (ChiCTR-IOR-16008362) and will be reported in compliance with the CONSORT statement (www.consort-statement.org) [31] as well as STRICTA (Standards for Reporting Interventions in Clinical Trials of Acupuncture) [32].

### Participants

Patients with moderate TH will be recruited from the neurosurgery unit at Huaxi Hospital in China. The diagnosis of TH and the side of the hemorrhage will be determined based on computer tomography. TH volume will be calculated by the neurosurgeon for all patients. Patients who meet eligibility criteria will be enrolled in the study, and written informed consent will be obtained prior to their enrollment.

### Subject enrollment

The nurses responsible for the neurosurgery patients at Huaxi Hospital will be thoroughly educated regarding moderate TH. Patients and/or their legal guardians will be able to contact the project leader at any time should they desire additional information. After obtaining signed informed consent, the project leader will collect certain baseline information (including age, diagnosis, side of hemorrhage (left or right), hematoma volume, medical history, CT report, etc..) and determine whether or not the patient meets the eligibility criteria for the trial or not. Only participants who meet the inclusion criteria and do not possess any of the exclusion criteria will be enrolled. A total of 488 patients with TH who are admitted to the neurosurgical unit of our hospital will be enrolled in the trial.

### Randomization and blinding

Randomization of subjects to the study and control groups will be computer-generated, using the Package for Encyclopaedia Medical Statistics 3.1 (PEMS 3.1) software. Stratified block randomization will not be performed. Concealed allocation will be achieved by having an assigned researcher not to have any contact with patients. Group assignments will be placed in opaque sealed envelopes. Subjects with 10–15 cc left TH, 10–15 cc right TH, 15–30 cc left TH, and 15–30 cc right TH will thus be assigned to either an acupuncture plus conventional treatment group or a conventional treatment alone group, in a 1:1 ratio based on the size and side of their hemorrhage. The primary researchers will be blinded to the type of intervention that each patient has received. The acupuncture practitioners will not provide any clues regarding group assignments to either the researchers or to the statistician.

### Inclusion criteria

Patients with ICH who meet the following inclusion criteria will be enrolled in the trial:First ever TH verified by computer tomography (CT)Moderate TH (10 ~ 30 ml);Unilateral primary TH;Hematoma originating and confined to the thalamus;Age between 18 and 70 years;Acupuncture treatment can be applied within 72 h after TH;Voluntarily willing to sign informed consent.Right handed.All bleeding has stopped at the time of acupuncture initiation.

### Exclusion criteria

Patients meeting any of the following criteria will be excluded from the study:Traumatic TH;Bilateral TH;Hematoma originates in another location and extends to the thalamus or hematoma originates in the thalamus and extends beyond the thalamus;Other areas of cerebral infarction, cerebral hemorrhage, or tumor on admission CT/MRI;Unable to determine the location of the origin of the hematoma on admission CT;Minor TH (<10 ml) or major TH (>30 ml);Heart, liver, or renal failure;Refusal to sign written informed consent;Unable to undergo randomized enrollment.Left handed.Continued bleeding at the time of acupuncture administration.

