### Procedure

Eligible patients will be randomized to either study groups (acupuncture plus conventional treatment) or control groups (conventional treatment alone) based on the size and side of their TH. After successful randomization, neurological assessments will occur at four time points: before treatment sessions begin, 30 days after onset of TH, at the end of treatment (6 weeks), and 90 days after onset of TH.

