### Control group

Subjects in the control groups will not receive acupuncture treatments. They will receive conventional TH treatments only. Control group participants will then be assessed neurologically at each follow-up visit.

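### The bleeding criteria are timed at the start of acupuncture, an event after randomization that only one arm reaches, so read literally they permit one-sided exclusion

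*Protocol article*

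**What the plan says.** Two criteria in the protocol article concern bleeding. The Inclusion criteria require "All bleeding has stopped at the time of acupuncture initiation". The Exclusion criteria list "Continued bleeding at the time of acupuncture administration", under the lead-in "Patients meeting any of the following criteria will be excluded from the study".

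Other sections place the eligibility decision earlier. Under Subject enrollment, the project leader collects baseline information after consent in order to "determine whether or not the patient meets the eligibility criteria for the trial or not", and "Only participants who meet the inclusion criteria and do not possess any of the exclusion criteria will be enrolled". The Procedure section then says "Eligible patients will be randomized to either study groups (acupuncture plus conventional treatment) or control groups (conventional treatment alone").

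According to the Acupuncture section, needling starts within 72 h of onset. The Control group section states "Subjects in the control groups will not receive acupuncture treatments", and Table 2 (item 6b) rules out a sham procedure. On imaging, Study design says "CT imaging will be performed on admission and at 90 days follow up".

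**The concern.** An eligibility criterion should be answerable for every candidate before allocation is known. These two refer to the patient's state when acupuncture begins. That moment lies after randomization, and in the control arm it never comes.

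A patient judged stable at screening may be found to be bleeding at the first session. If that patient was allocated to acupuncture, the literal text says to exclude. For the same patient allocated to control, the criterion has nothing to act on.

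The Background names haematoma enlargement as a major contributor to the high morbidity and mortality of intracerebral haemorrhage. Losing such patients from the acupuncture arm alone would make that arm look better on NIHSS, on a modified Rankin score of 3–6 and on the rate of surgery, even if acupuncture did nothing.

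**Working it through.** **Step 1: the sections side by side.**

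| Question | Where | Answer |
|---|---|---|
| When is bleeding judged? | Inclusion and Exclusion criteria | When acupuncture starts or is given |
| When is eligibility settled? | Subject enrollment; Procedure | Before randomization |
| When does acupuncture start? | Procedure; Acupuncture | After randomization, within 72 h of onset |
| Do controls reach that moment? | Control group; Table 2, item 6b | No: neither acupuncture nor sham |
| What follows from meeting the criterion? | Exclusion criteria, lead-in | Exclusion from the study |

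The first two rows cannot both hold as worded, because no acupuncture has started when eligibility is decided. The last three rows show why following the first row literally would act on one arm only.

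**Step 2: the plan's own figures, used only as a scale.** Sample size calculation gives SD 4.2, difference 2.3, 80% power, α = 0.05, 10% non-adherence and 3% loss. The Statistical analysis section makes tests two-sided.

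- n per arm = 2 × (1.960 + 0.842)² × 4.2² / 2.3² = 52.3, rounded up to 53.
- Attrition: 53 / 0.87 = 60.9, rounded up to 61.
- Eight groups: 8 × 61 = 488, which matches the stated total.

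The sample size is not in question. It supplies the SD, the target difference and the 61 per arm used below.

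**Step 3: how large a one-sided exclusion could be.** Two inputs are needed that the document does not give, so both are assumptions:

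- f, the share of acupuncture patients excluded for continued bleeding: 3–10%.
- g, how many NIHSS points worse such patients score: 4–6.

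Formulas, with no true effect and N = 61 per arm in one size-by-side stratum:

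- Bias = f × g
- SE = 4.2 × √(1/(N(1 − f)) + 1/N)
- Type I error = P(|Z + bias/SE| > 1.96)

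| f | g | Bias (points) | Share of 2.3 | SE | Type I error |
|---|---|---|---|---|---|
| 3% | 4 | 0.12 | 5% | 0.766 | 0.053 |
| 5% | 6 | 0.30 | 13% | 0.770 | 0.068 |
| 10% | 6 | 0.60 | 26% | 0.781 | 0.120 |

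Two simplifications apply. The SD is held at 4.2 in both arms, and every comparable control is taken to stay in the analysis. With 53 per arm, the number left after the planned attrition, the last row falls from 0.120 to 0.110.

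**The case against.** The strongest reply is that both criteria sit in the entry lists and would simply be applied at screening. The Inclusion criteria contain another item that mentions acupuncture, feasibility within 72 h, and it can be judged for every candidate. On that reading, someone known to be bleeding at screening is turned away before allocation, whichever arm would have followed. This stands against a stronger claim that a reader might infer: that the criterion can be failed only after allocation and only in the acupuncture arm. The document does not support that. The reply does not cure the wording, however. The 72 h item is prospective, whereas the bleeding items name the state at the moment of treatment, and a patient can be stable at screening and bleeding at the first session.

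A reader might also infer that the plan actually removes the worst patients from one arm. No section says so. Continued bleeding is not among the six Dropout criteria, and the items on deterioration and on the principal investigator's judgement can remove patients from either arm. The assumption that every comparable control is kept is therefore not established. But those items turn on whether participation can continue. They supply no matching bleeding check in controls.

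The Procedure section gives all randomized patients an assessment before treatment sessions begin, so nominal treatment times do exist in both arms. That assessment comes after randomization, so it does not make the criterion a pre-allocation one.

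The article names CT on admission and at 90 days but does not say that no other scan is done. How cessation of bleeding is confirmed is a detail that an article may leave to the full protocol, and no weight is put on it here.

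Finally, the size rests on assumed f and g, and the low case is negligible. Pooling all strata would give larger type I errors, but the document states no pooled test and its sample size matches a single stratum, so only per-stratum figures are used.

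**Conclusion.** The point holds as a defect of wording with a possible bias attached. The two bleeding criteria are tied to an event that follows randomization and occurs in one arm. They conflict with the sections that settle eligibility beforehand and, followed literally, they permit one-sided exclusion in favour of acupuncture. That such exclusion will occur is not shown.

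Its size cannot be derived from the document. Under the assumed ranges the bias runs from 0.12 to 0.60 NIHSS points, 5–26% of the planned difference, with a per-stratum type I error of about 5–12% against the nominal 5%. At the lower end it hardly matters. At the upper end it would matter in a trial that looks for 2.3 points.

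**What to change.** Reconcile the Inclusion and Exclusion criteria with Subject enrollment and Procedure:

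1. Reword both bleeding items so that status is judged once, before the allocation envelope is opened, on the same available information for every candidate.
2. Add one sentence to the analysis: a patient found to be bleeding after randomization stays in the trial and is analysed in the allocated arm, whatever is decided clinically about needling.

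Neither change sets a clinical rule on when needling is given or withheld. The cost is two reworded criteria and one sentence. The sample size stays at 488, and using information already available calls for no extra study scan. The small downside is that a few acupuncture patients may be analysed without having been needled, which slightly dilutes any true effect.

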### Procedure

Eligible patients will be randomized to either study groups (acupuncture plus conventional treatment) or control groups (conventional treatment alone) based on the size and side of their TH. After successful randomization, neurological assessments will occur at four time points: before treatment sessions begin, 30 days after onset of TH, at the end of treatment (6 weeks), and 90 days after onset of TH.

### Intervention

Participants in both groups will receive conventional Western medical treatments as recommended by the guidelines for the management of spontaneous intracerebral hemorrhage including blood pressure management, ICP monitoring, appropriate prophylaxis, and surgical treatment as necessary for life-threatening hemorrhages [2]. In addition to conventional treatment, patients in the study group will receive 36 sessions (once a day, 6 days a week for 6 weeks) of acupuncture.

### Acupuncture

Acupuncture treatment will be started within 72 h after TH onset, and applied once a day, 6 days a week for 6 weeks (a total of 36 sessions). The sessions will be performed by an experienced acupuncture doctor with over 10 years of working experience and 7 years of acupuncture training. This doctor will also receive training prior to the start of the trial. The acupuncture protocol was designed by a Sichuan University Huaxi Hospital professor with more than 25 years of practical experience, in accordance with guidelines from published papers and clinical experience. It will follow the Standards for Reporting Interventions in Clinical Trials for Acupuncture 2010 checklist, as shown in Table 1. Acupuncture points are identified by the point location method as described by the World Health Organization (WHO standard) [33].

**Table 1 Tab1:** Acupoints to be used in the study

Acupoint	Location	Major indication and function
MS 5 (Dingzhonxian)	At the top of the head, along the middle line of the head, connecting DU 20 to DU 21.	Prolapse, sacral and lumbar problems, paralysis, cortical polyuria, gastroptosis, hyperostosis, hypertension
MS 6 (Dingnieqianxiexian)	1 cun anterior from DU 20 to GB 6.	Treats motor function disorders
MS 7 (Dingniehouxiexian)	1 cun posterior to MS6, from DU 20 to GB 7.	Treats sensory function disorders
LI15 (Jian Yu)	On the shoulder girdle, in the depression between the anterior end of the lateral border of the acromion and the greater tubercle of the humerus.	Shoulder pain, paralysis
LI11 (Qu Chi)	On the lateral aspect of the elbow, at the midpoint of the line connecting LU5 with the lateral epicondyle of the humerus.	Upper extremity palsies, relaxes and strengthens tendons
SJ5 (Wai Guan)	On the posterior aspect of the forearm, at the midpoint of the interosseous space between the radius and the ulna, 2 B-cun proximal to the dorsal wrist crease.	Tinnitus, paralysis of the arms, upper extremity pain;
LI4 (He Gu)	On the dorsum of the hand, in the depression radial and proximal to the second metacarpophalangeal joint.	Spasm in the fingers
ST34 (Liang Qiu)	On the anterolateral aspect of the thigh, between the vastus lateralis muscle and the lateral border of the rectus femoris tendon, 2 B-cun superior to the base of the patella.	Gastrospasm, leg muscle atrophy
ST36 (Zu San Li)	On the anterior aspect of the leg, on the line connecting ST35 with ST41, 3 B-cun inferior to ST35.	Constipation or diarrhea, paralysis of the lower limbs
GB34 (Yang Ling Quan)	On the fibular aspect of the leg, in the depression anterior and distal to the head of the fibula.	Inhibited ability to flex and stretch
SP6 (San Yin Jiao)	On the tibial aspect of the leg, posterior to the medial border of the tibia, 3 B-cun superior to the prominence of the medial Malleolus.	Irregular menstruation, paralysis of the lower limbs
LV3 (Tai Chong)	On the dorsum of the foot, between the first and second metatarsal bones, in the depression distal to the junction of the bases of the two bones, over the dorsalis pedis artery.	Hypertension, paralysis

Both scalp and body acupuncture will be performed in this trial. The parameters for scalp acupuncture will be as follows: two or three needles penetrating through the top midline, the motor region of the affected side, and the sensory region on the side of the lesion. The acupoints on the affected side of the body only and not on the contralateral side will be as follows: LI15 (Jian Yu), LI11 (Qu Chi), SJ5 (Wai Guan), and LI4 (He Gu) in the upper extremity; ST34 (Liang Qiu), ST36 (Zu San Li), GB34 (Yang Ling Quan), SP6 (San Yin Jiao), and LV3 (Tai Chong) in the lower extremity (Table 1). Additional acupoints will be added as follows: RN23 (Lian Quan), bilateral GB20 (Feng Chi), and ST9 (Ren Ying) for dysphagia; ST6 (Jia Che) and ST5 (Di Cang) on the affected side for facial paralysis (Table 2).

**Table 2 Tab2:** Interventions details according to Standards for Reporting Interventions in Clinical Trials of Acupuncture (STRICTA) guidelines

Item	Detail	Detail response
1. Acupuncture rationale (Explanations and examples)	1a) Style of acupuncture (e.g. Traditional Chinese Medicine, Japanese, Korean, Western medical, Five Element, ear acupuncture, etc)	Traditional needle acupuncture
	1b) Reasoning for treatment provided, based on historical context, literature sources, and/or consensus methods, with references where appropriate	Selected traditional acupuncture points in the 12 meridian system and scalp points based on literature review and clinical experience
	1c) Extent to which treatment was varied	No variation
2. Details of needling (Explanations and examples)	2a) Number of needle insertions per subject per session (mean and range where relevant)	13–19 insertions per session
	2b) Names (or location if no standard name) of points used (uni/bilateral)	Scalp points: motor region and sensory region, unilateral on the side of the lesion Acupoints on limbs:LI15 (Jian Yu), LI11 (Qu Chi), SJ5 (Wai Guan), LI4 (He Gu), ST34 (Liang Qiu), ST36 (Zu San Li), GB34 (Yang Ling Quan), SP6 (San Yin Jiao), LV3 (Tai Chong),all unilateral on the affected side Modification: for dysphagia, GB20 (Feng Chi), RN23 (Lian Quan), and ST9 (Ren Ying); for facial paralysis, ST6 (Jia Che) and ST5 (Di Cang), unilateral on the affected side
	2c) Depth of insertion, based on a specified unit of measurement, or on a particular tissue level	Depth of needle insertion is at least 5 to 10 mm
	2d) Response sought (e.g. *de qi* or muscle twitch response)	De-qi sensation felt by practitioner and subject
	2e) Needle stimulation (e.g. manual, electrical)	Manual
	2f) Needle retention time	30 min
	2 g) Needle type (diameter, length, and manufacturer or material)	Needles: 0.25 × 40 mm, stainless steel (Huatuo brand, made by Suzhou Medical Appliances, China)
3. Treatment regimen (Explanations and examples)	3a) Number of treatment sessions	36 sessions
	3b) Frequency and duration of treatment sessions	6 times per week, interval of 1 day between sessions
4. Other components of treatment (Explanations and examples)	4a) Details of other interventions administered to the acupuncture group (e.g. moxibustion, cupping, herbs, exercises, lifestyle advice)	None
	4b) Setting and context of treatment, including instructions to practitioners, and information and explanations to patients	The same practitioner will treat every subject every session at the patient’s bedside
5. Practitioner background (Explanations and examples)	5) Description of participating acupuncturists (qualification or professional affiliation, years in acupuncture practice, other relevant experience)	Licensed Traditional Chinese medicine doctor at Huaxi Hospital of Sichuan University with more than 10 years of acupuncture treatment experience
6. Control or comparator interventions (Explanations and examples)	6a) Rationale for the control or comparator in the context of the research question, with sources that justify this choice	No acupuncture will be performed on the control group
	6b) Precise description of the control or comparator. If sham acupuncture or any other type of acupuncture-like control is used, provide details as for Items 1 to 3 above.	No sham acupuncture will be performed on the control group

Stimulation will be applied to both the scalp and body acupoints until the patient experiences de qi (obtains qi). A patient’s experience of de qi may take on multiple unique manifestations at the needle site itself and/or around the site of needle manipulation including soreness, aching, numbness, tingling, and even warmth.

Huatuo brand needles (size 0.25 mm × 40 mm) made by Suzhou Medical Appliances in Suzhou, Jiangsu province, China, will be used to perform the acupuncture treatments. Electrical stimulation of acupuncture needles will be done at low frequency (1–3 Hz) in order to ensure patient comfort.

